## **6. SUBJECT SELECTION**

### **6.1 PLANNED NUMBER OF SUBJECTS**

A total of **390 patients** will be enrolled into this study (130 patients in control group A and 260 patients in experimental group B).

### **6.2 SCREENING CRITERIA**

Before any protocol-specific procedures are started, written informed consent of the patient must be obtained and documented.

#### **Inclusion criteria:**

- Patients infected with HIV-1, as documented by a positive HIV-1 antibody test and/or a documented positive PCR for HIV-1 RNA.
- Patients on antiretroviral triple therapy containing any boosted PI.
- Patients with an undetectable viral load, defined as < 50 copies/mL in the past 6 months.
- Males or females aged  $\geq 18$  years.
- For women of childbearing age, a negative urine pregnancy test at the screening visit.
- Patients who have given written informed consent before undergoing any study-specific screening procedure.

#### **Exclusion criteria:**

- Patients with documented record, in the resistance accumulated genotyping, of mutations that confers loss of susceptibility to LPV/r. Or, in the absence of genotyping, evidence of having failed to therapy with protease inhibitors (PI)

- Patients with a CD4 cell nadir <100 cel/ $\mu$ L.
- Patients who cannot be treated with LPV/r for any reason.
- History of psychiatric disorders such as depressive syndrome, schizophrenia, or psychotic disease. Known history of drug addiction or chronic alcohol consumption that contraindicates participation in the study in the investigator's criterion.
- Pregnant or nursing women or women of childbearing age not using an adequate contraceptive method according in the investigator's criterion.
- Current active opportunistic infection or documented infection within 4 weeks of screening.
- Patients in whom modification or withdrawal of any component of the current antiretroviral triple therapy is planned due to serious toxicities related to any component of such therapy. Patients in whom investigators consider that antiretroviral medication should be changed for any reason in the next 6 months.
- Renal disease with creatinine clearance < 60 mL/min.
- Concomitant use of drugs contraindicated with LPV/r such as rifampin, dihydroergotamine, ergotamine, methylergonovine, cisapride, St. John's wort, lovastatin, simvastatin, pimozide, midazolam, and triazolam.
- Concomitant use of nephrotoxic or immunosuppressive agents.
- Patient on current treatment with systemic corticosteroids, interleukine-2, or chemotherapy.
- Patients treated with other investigational agents.
- Patients with acute hepatitis.
- Any disease that, in the investigator's judgment, contraindicates patient participation in the study.

### **6.3 NON-COMPLIANCE WITH SCREENING CRITERIA**

All patients should meet all inclusion criteria and none of the exclusion criteria. To prevent enrollment of non-eligible patients, any doubt should be consulted with the sponsor. If a patient does not meet the eligibility criteria and is inadvertently enrolled into the study, this should be reported to the study sponsor so that patient continuation in the study may be assessed, evaluating the risks and benefits for the patient and ensuring maximum safety.

#### **6.4 TREATMENT DISCONTINUATION. STUDY WITHDRAWAL.**

Any patient will be withdrawn from the study in the following circumstances:

- At the request of the patient.
- Serious adverse event or unacceptable toxicity.
- Pregnancy.
- When the investigator thinks that a change in treatment not planned in the protocol is required in the best interest of the patient.

The date and reasons for any early discontinuation will be recorded in the Case Report Form (CRF) and considered in the final assessment.

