### **Intolerance**

A serious adverse effect as defined in section 7.7 (Scheme modification criteria for toxicity).

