#### **8.2.5 Early study discontinuation**

In the event of early discontinuation, the subject should return to the site as soon as possible (preferably within 72 hours of study drug discontinuation) for an early study discontinuation visit. The following assessments should be completed at that visit:

- Physical examination (vital signs, weight).
- Complete blood count (red blood cell count, white blood cell count and differential, and platelet count).
- Fasting chemistry profile (alkaline phosphatase, ALT, AST, GGT, total bilirubin, creatinine, glucose, potassium, sodium, uric acid, lipid profile (total cholesterol, HDL-C, LDL-C, VLDL-C, triglycerides).
- CD4 cell count
- HIV-1 RNA in plasma: If the patient shows at any time a detectable viral load (> 50 copies/mL), the test should be repeated within 2 weeks for confirmation
- Quality of life questionnaires (MOS-HIV and EQ-5D)

- Questionnaires for assessing treatment adherence (GEEMA and VAS)
- Questionnaire for assessing treatment satisfaction (CESTA)
- Concomitant medications.
- Adverse events

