### **8.2.6 Criteria for treatment discontinuation or modification**

Study medication should be discontinued if the following occurs:

- Underlying disease that may significantly affect assessments of clinical status in the investigator's judgment.
- Unacceptable toxicity (toxicity that compromises the ability to continue with the protocol-specific procedures).
- At the request of the subject.
- Pregnancy
- Therapeutic failure, defined as 2 VL measurements > 500 copies/mL at least 2 weeks apart in the experimental group and/or genotyping with PI mutations that prevent continued treatment with LPV/r monotherapy.

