#### **Serious adverse event (SAE): definition and reporting procedure**

A serious adverse event (SAE) is any event that is fatal or life-threatening, requires or prolongs patient hospitalization, causes persistent or significant incapacity or disability, is a congenital anomaly or birth defect, or is a clinically significant event.

Clinically significant events are those that may not be immediately life-threatening, but are clearly clinically significant. They may jeopardize the subject or require intervention to prevent any serious outcome. Overdose or abuse of a drug will usually be considered as serious.

|                                        |                                                                                                                                                                                                                                     |
|----------------------------------------|-------------------------------------------------------------------------------------------------------------------------------------------------------------------------------------------------------------------------------------|
| Death                           | An event that results in patient death.                                                                                                                                                                                             |
| Life-threatening                | An event that, in the investigator's judgment, could have caused the immediate death of the patient if no medical intervention had occurred. This does not include the events that could have been fatal had they been more severe. |
| Hospitalization                 | An event that requires hospital admission, regardless of hospitalization time. This does not include emergency room visits or the stay at an outpatient center.                                                                     |
| Prolongation of hospitalization | An event that occurs while the study subject is hospitalized and prolongs hospital stay.                                                                                                                                            |

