#### **Statistical analysis**

Baseline characteristics of study groups will be compared using an analysis of variance (ANOVA). The mean, median, standard deviation, and range will be provided for continuous variables, and the distribution of absolute frequencies and percentages will be given for discrete variables. When required, 95% confidence intervals will be calculated. Discrete variables will be compared using a Chi-square test.

For quality of life analysis, the primary population will include all patients with data available from baseline up to at least one post-baseline visit (e.g. the intention-to-treat population).

In case of patient abandonment is taken as a post-treatment evaluation the one obtained at the time of abandonment. If there is no post-treatment evaluation as a neutral value, baseline observation value will be carried forward until month 24 or the time of abandonment (Baseline Observation Carried Forward).

The main deadline to study results will be week 24 of the study. An analysis of covariance (ANCOVA) will be used for quality of life comparison. The model will include the baseline values for the items in the MOS-HIV questionnaire, age and sex as covariates, in the control and study groups. For primary endpoint analysis, the values in the MOS-HIV and EQ-5D questionnaires in the different weeks as compared to baseline will be provided for each treatment group.

An analysis of covariance (ANCOVA) will be used for comparisons between both treatment groups.

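### Section 6.4 ends study participation, not only treatment, for any SAE, unacceptable toxicity or unplanned treatment change, so an exit or baseline score stands in for week-24 quality of life; the stopping rules also disagree

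*Protocol*

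**What the plan says.** **Withdrawal.** Section 6.4 opens with "Any patient will be withdrawn from the study in the following circumstances". The list includes "Serious adverse event or unacceptable toxicity" and "When the investigator thinks that a change in treatment not planned in the protocol is required in the best interest of the patient". Neither relatedness nor severity qualifies the SAE item. The SAE definition in section 9.1 covers "An event that requires hospital admission, regardless of hospitalization time", and the same section says that an adverse event need not be caused by treatment.

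**What is collected afterwards.** Section 8.2.5 calls the patient to an early discontinuation visit, "preferably within 72 hours of study drug discontinuation". MOS-HIV and EQ-5D are scheduled only at baseline and at week 24 or that exit visit (sections 8.2.1, 8.2.3 and 8.2.5). Later contacts are a 30-day safety telephone call (8.2.4) and, for some therapeutic failures, a visit 4 weeks after the end-of-study visit (7.2). Neither is stated to include quality of life.

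**Analysis.** The primary endpoint in 8.1.1 is the change at 24 weeks. Section 12.4 says: "In case of patient abandonment is taken as a post-treatment evaluation the one obtained at the time of abandonment". If there is no such evaluation, baseline is carried forward. Section 12.1 calls the main population intention-to-treat and says that it should reflect usual practice.

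**Other versions of the stopping rule.** The Intolerance paragraph of section 7.2 reads: "A serious adverse effect as defined in section 7.7 (Scheme modification criteria for toxicity". Section 8.2.6, which governs study medication, lists "Unacceptable toxicity (toxicity that compromises the ability to continue with the protocol-specific procedures" and does not list an SAE as such.

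**The concern.** The trial asks how quality of life compares at 24 weeks between patients assigned to monotherapy and patients kept on triple therapy. For a patient withdrawn under 6.4, the analysed value was measured at another time or is the baseline value. If such exits were equally common and alike in both arms, the difference between arms would suffer little. The protocol expects otherwise. Its sample-size section expects more diarrhoea among patients starting the new regimen, and section 12.1 (A.2) expects more abandonment there because of an adverse event.

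The SAP cannot repair this alone. It can change an imputation rule, but it cannot recover questionnaires that were never given. If sites also read the stopping rules differently, the number and kind of exits will vary between sites for reasons unrelated to the treatments.

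**Working it through.** **1. The plan's own target.** Section 12 assumes means of 61.84 and 68.02, so the difference is 68.02 − 61.84 = 6.18. With SD 20, two-sided alpha 0.05, power 80% and 1:2 allocation, the calculation gives 124 control and 248 experimental patients, 372 in all. This matches the plan, so 6.18 points is a fair yardstick.

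**2. Path of a withdrawn patient.**
- Section 6.4: leaves the study.
- Section 8.2.5: completes MOS-HIV and EQ-5D at the exit visit, timed from stopping the drug.
- Sections 8.2.3 and 8.2.4: no quality-of-life assessment at week 24.
- Section 12.4: the exit score, or baseline, becomes the post-treatment value.
- Section 8.1.1: the endpoint is nevertheless the 24-week change.

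The secondary population A.2 drops patients who left for adverse events, and the per-protocol population keeps only completers. Neither supplies the missing week-24 score.

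**3. Illustration of size.** The documents give no SAE rate, exit rate or exit score, so the inputs are assumptions. Let D be the excess share of exits in the experimental arm, and G the gap between the exit score and the score the same patient would have given at week 24, taken as equal in both arms. The shift in the arm difference is D × G.
- Low: 0.03 × 5 = 0.15 points; 0.15 / 6.18 = 2%.
- High: 0.10 × 15 = 1.5 points; 1.5 / 6.18 = 24%.

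For scale, the unadjusted standard error at 130 and 260 patients is 20 × √(1/130 + 1/260) = 2.15, so the high end is 1.5 / 2.15 = 0.7 standard errors.

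**4. The stopping rules side by side.**

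| Place | What ends | SAE or toxicity trigger |
|---|---|---|
| 6.4 | Study participation | Any SAE, or unacceptable toxicity |
| 7.2, Intolerance | Study participation (listed as a withdrawal criterion) | A serious adverse effect defined in section 7.7; section 7 ends at 7.4 |
| 8.2.6 | Study medication | Toxicity that prevents protocol procedures; SAE not listed |

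On virological failure, 8.2.6 stops study medication in the experimental group after two viral loads above 500 copies/mL and/or on PI mutations. Section 7.2 lets such a patient without LPV/r resistance be reinduced with the previous nucleosides and remain in the study.

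**The case against.** The strongest reply is that the exit-value rule is prespecified, that A.2 and the per-protocol population give alternative views, and that a score observed at week 24 after stopping monotherapy may partly reflect a return to triple therapy. Making it primary therefore changes the question. This stands in part: it is a choice of estimand. But the protocol has already chosen a 24-week endpoint, an intention-to-treat label and an aim of reflecting usual practice, and these fit the observed week-24 score better than an exit score. Keeping the exit-value rule as a sensitivity analysis preserves the other view.

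It can also be said that 6.4 concerns the study and 8.2.6 the medication, so different lists need not conflict. That is fair as far as it goes. However, 8.2.5 treats stopping the drug as early study discontinuation, and the reference to section 7.7 leads nowhere.

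Some stronger readings are tempting but not supported:
- *Withdrawn patients use up the 7% loss allowance.* Section 12.4 keeps them in the analysis with an exit or baseline value.
- *The exit score is a snapshot of the acute event.* The 72 hours run from stopping the drug, not from the event, and are only preferred. Most MOS-HIV items look back 4 weeks; EQ-5D asks about the same day.
- *Every failure of monotherapy removes the patient.* Reinduced patients stay in the study under 7.2.
- *Virological and immunological data are lost.* HIV RNA and CD4 are measured at exit; only the week-24 values are missing.
- *The bias runs against monotherapy.* Low exit scores would push that way, but carrying baseline forward sets the change to zero. The net direction is unknown.

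**Conclusion.** The point holds in a limited form. Section 6.4 ends follow-up for reasons that need not end it, no week-24 quality of life is collected afterwards, and a mistimed or baseline value enters the primary analysis. Imbalance between arms is likely on the protocol's own expectations. The range of 0.15 to 1.5 points is illustration only and rests wholly on the assumed exit imbalance and score gap. Its low end is negligible, and its high end needs both assumptions at their upper limits. The case for change rests less on a demonstrated bias than on the fact that the data are cheap to collect and cannot be recovered later. The disagreement between 6.4, 7.2 and 8.2.6 is a separate defect that can be read directly from the text.

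**What to change.** 1. In 6.4, 7.2 and 8.2.6, separate stopping assigned treatment from leaving the study.
2. State that every randomised patient who has not withdrawn consent completes MOS-HIV, EQ-5D, HIV RNA and CD4 at week 24, whatever treatment is then taken. Keep the exit-visit assessments as additional data.
3. Use the observed week-24 score in the intention-to-treat primary analysis. Keep the exit-value and baseline-carried-forward rule for patients with no week-24 value, and repeat the analysis under the present rule as a sensitivity analysis.
4. Reconcile 6.4, 7.2 (Intolerance) and 8.2.6 on SAEs and toxicity, and correct the reference to section 7.7. Reconcile 7.2 with 8.2.6 on two viral loads above 500 copies/mL without resistance. Which clinical rule should apply is for the sponsor and investigators.

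The cost is protocol wording and one extra assessment for those who stop early, expected to be few. The trade-off is that some of their week-24 scores will reflect a later regimen, which the plan should say openly.

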#### **6.5 ESTIMATED DURATION OF THE RECRUITMENT PERIOD**

Recruitment will start once the relevant approvals have been obtained. The planned duration of the recruitment period is 6 months. The planned total study duration is 12 months.

## **7. DESCRIPTION OF TREATMENT**

### **7.1 DRUG ADMINISTRATION SCHEME**

Patients will be randomized to one of the following treatment groups:

**Control group (A):** Patients will continue on antiretroviral triple therapy based on any PI boosted with ritonavir.

Medication will be administered in accordance to the relevant prescribing information.

**Experimental group (B):** Switch to LPV/r monotherapy.

Kaletra® alone, two tablets twice daily.

### **7.2 Patient withdrawal criteria**

#### **Therapeutic failure**

Patients who meet therapeutic failure criteria will be withdrawn from the study. These criteria are defined as follows:

1. In patients receiving triple therapy randomly assigned at baseline, documented virological failure, i.e. the presence of a viral load greater than 500 copies/mL on 2 occasions 15 days apart, is considered as therapeutic failure.
2. Patients assigned to maintenance with LPV/r alone who reach the virological failure criterion will be considered as therapeutic failures if protease gene mutations exist, so that the patient cannot be reinduced with nucleosides and would discontinue the study because of the need of a therapy not based on LPV/r.
3. However, patients assigned to maintenance with LPV/r alone can be reinduced with the same nucleosides as withdrawn if no documented resistance to LPV/r exists. Thus, the following specific situation (a+b+c) will NOT be considered as therapeutic failure and will not lead to study discontinuation:
  - a) A patient in the maintenance arm with LPV/r alone has a viral load greater than 500 copies/mL on 2 occasions 15 days apart.
  - b) The genotypic resistance test shows no resistance to LPV/r.
  - c) The patient is reinduced with the same nucleosides as received before study entry and completes the follow-up period with an undetectable VL.

If this situation has occurred, and once patients are reinduced, they will be considered as therapeutic failures when the following conditions are met:

- 4 weeks after reinduction, viral load has not decreased by at least one decimal logarithmic unit
- and/or does not become undetectable again (<50 copies/mL) at 16 weeks of reinduction
- or if once on triple therapy they experience virological failure again.

In patients in whom a viral load ranging from 50-500 copies/mL is obtained, the above procedure will be followed.

After this viral load has been confirmed three times (2 weeks, 2 weeks, and 4 weeks), the following will be done:

- Patients in the monotherapy group and with no lopinavir resistance will be reinduced with the same nucleosides and the procedure in the previous paragraphs will be followed.
- Patients on triple therapy or in the monotherapy group but with lopinavir resistance: these will be considered as therapeutic failures, and after designing rescue treatment a follow-up visit will be scheduled 4 weeks after the end of study visit.

Annex 1 to the protocol provides a detailed scheme of management of patients with virological failure.

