LPV/r is characterized by a very high pharmacological and genetic barrier. Trough plasma levels of LPV/r are more than 70-fold higher than the EC50 for wild-type HIV. Occurrence of resistance to LPV/r requires accumulation of mutations in the protease gene. The EC50 for wild-type HIV starts to show a clinically significant increase from five mutations [10-11]. In

study 863, none of the patients treated with LPV/r with a viremia rebound to more than 400 copies/mL developed mutations in the protease gene [12].

In addition, the new formulation of LPV/r as tablets decreases pill overload and also eliminates the requirement of refrigeration. Administration of medication with food is not required either [9].

Together, these advantages promote simplification of antiretroviral therapy and a potential improvement in adherence. In recent years, data have been reported on use of LPV/r monotherapy as starting treatment [13], as maintenance after initial therapy [14], and as maintenance following HAART with undetectability sustained for at least 6 months [15-17].

The third approach is the one that has been shown to date to be safest for use of LPV/r as monotherapy, based on reported data from the OK04 study (a randomized, comparative study on 200 patients) at 48 weeks [15] and at 96 weeks [18].

In another open label study (MONARK) in which naïve patients were randomized to receive monotherapy based on LPV/r® or standard antiretroviral triple therapy using LPV/r (Kaletra®)+ AZT/3TC (Combivir®), virological efficacy was similar in both groups at 48 weeks of treatment even in patients in the monotherapy group who had episodes of lower viremia levels [5]. In addition, the mean total symptoms reported and the number of symptoms causing discomfort were significantly higher in the triple therapy group as compared to the monotherapy group (relative risk 1.3 and 1.4; P= 0.001 and P= 0.0003 respectively), and the proportion of patients with a positive perception of their overall quality of life increased in the monotherapy group from 32% at baseline to 68% at 48 weeks of study (P<0.0001), and in the triple therapy group from 46% to 59% (P= 0.38) [5].

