### **Baseline visit:**

If laboratory data for confirming screening criteria have been obtained within two months of study recruitment and are available, the screening visit may be the same as the baseline visit.

The study drugs should start to be taken within 24 hours of the baseline visit. The following assessments should be available at the baseline visit:

- Physical examination (vital signs, height and weight).
- Quality of life questionnaires (MOS-HIV and EQ-5D)
- A negative urine pregnancy test for women of childbearing age.

- Complete blood count (red blood cell count, white blood cell count and differential, and platelet count).
- Fasting chemistry profile (alkaline phosphatase, ALT, AST, GGT, total bilirubin, creatinine, glucose, potassium, sodium, uric acid, lipid profile (total cholesterol, HDL-C, LDL-C, VLDL-C, triglycerides).
- CD4 cell count
- HIV-1 RNA in plasma: This will be measured in real time at the site using the standard virological methods at each site. The same methods should be used throughout the study for each subject.
- CESTA questionnaire to assess satisfaction with antiretroviral treatment.
- GEEMA questionnaire to assess treatment adherence
- VAS to assess treatment adherence
- Recording of concomitant medication
- Adverse events

Once the baseline visit procedures and assessments are reviewed, subjects will be centrally randomized at the study data center after data are received.

Patients randomized to group B will return for HIV RNA monitoring at treatment week 4 (+/- 2 days)

The following assessments should be completed at the **week 12 and week 24 visits or at the study discontinuation visit**. Study visits should be scheduled to occur within  $\pm 1$  week of the date specified for weeks 12 and 24, calculating the dates from the baseline visit:

- Physical examination (vital signs, weight).
- Complete blood count (red blood cell count, white blood cell count and differential, and platelet count)
- Fasting chemistry profile (alkaline phosphatase, ALT, AST, GGT, total bilirubin, creatinine, glucose, potassium, sodium, uric acid, lipid profile (total cholesterol, HDL-C, LDL-C, VLDL-C, triglycerides)
- CD4 cell count
- HIV-1 RNA in plasma: If the patient shows at any time a detectable viral load (> 50 copies/mL), the test should be repeated within 2 weeks for confirmation. Annex 1 provides suggestions for management of these cases
- Concomitant medication
- Adverse events

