#### **8.2.4 Post-treatment assessments**

Only if it has been reported any adverse event that may be under way in the last visit or, if the patient had presented a viral load > 50 copies / mL at that visit, a telephone follow-up call will be made after 30 days of last visit study to monitor safety.

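### Sections 7.2, 8.2.3, 8.2.5 and 8.2.6 give incompatible rules for a monotherapy patient who rebounds above 500 copies/mL, on what counts as therapeutic failure and on when the confirming sample is taken

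*Protocol*

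**What the plan says.** Four places in the protocol govern a rebound above 500 copies/mL in the monotherapy arm.

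- **7.2 Patient withdrawal criteria, Therapeutic failure.** Item 1 (triple therapy) describes virological failure as "the presence of a viral load greater than 500 copies/mL on 2 occasions 15 days apart", and item 3a repeats that interval for monotherapy. Item 2 says that monotherapy patients who reach the criterion "will be considered as therapeutic failures if protease gene mutations exist, so that the patient cannot be reinduced with nucleosides". The sentence goes on to say that such a patient leaves because a regimen not built on LPV/r is needed. Item 3 then says that monotherapy patients "can be reinduced with the same nucleosides as withdrawn if no documented resistance to LPV/r exists". Its condition b reads "The genotypic resistance test shows no resistance to LPV/r". A patient who meets conditions a to c, including an undetectable viral load at the end of follow-up, is expressly not a failure and is not withdrawn.
- **8.2.6 Criteria for treatment discontinuation or modification.** Study medication is to stop on therapeutic failure. For the experimental group this means two viral loads above 500 copies/mL, two weeks or more apart, and/or a genotype with PI mutations that preclude continued LPV/r monotherapy.
- **8.2.3 (week 12, week 24 or discontinuation visit) and 8.2.5 (early discontinuation).** For any viral load above 50 copies/mL, "the test should be repeated within 2 weeks for confirmation".
- **Annex 1.** 7.2 points to it as the detailed management scheme, while 8.2.3 describes its content as suggestions. Its flow chart is not reproduced in the text available for this review.

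**The concern.** A site with a rebounding monotherapy patient who has no LPV/r resistance can follow 7.2 item 3 and keep the patient in the trial on added nucleosides. It can also follow 8.2.6, declare failure and stop study medication. Separately, a site that retests promptly, as the visit section asks, produces a second value that does not meet the interval in either failure definition.

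This matters for the analysis because MOS-HIV and EQ-5D are collected only at baseline, week 24 and early discontinuation. Under 12.4, a patient who leaves contributes the evaluation made on leaving. Under 12.1, the per-protocol population consists of those who complete 24 weeks. The classification therefore decides whether the primary value is an exit score or a week-24 score, and whether the patient is in the per-protocol set. Reinduction is offered only in the monotherapy arm, so inconsistent handling falls on one side of the comparison.

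**Working it through.** The protocol gives no figure to reproduce here. The check sets the rules side by side.

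**Step 1: failure status.** Take a monotherapy patient with two viral loads above 500 copies/mL, validly spaced, who if reinduced ends undetectable. For 8.2.6, LPV/r resistance is taken to mean mutations that preclude LPV/r monotherapy.

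| Genotype | 7.2 item 2, literal | 7.2 item 3 | 8.2.6 read with or | 8.2.6 read with and |
|---|---|---|---|---|
| No protease mutation | not failure | not failure, stays | failure, medication stopped | not failure |
| Protease mutation, no LPV/r resistance | failure | not failure, stays | failure, medication stopped | not failure |
| LPV/r resistance | failure | does not apply | failure, medication stopped | failure, medication stopped |

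The rules agree on every reading only in the last row. In the first two rows, 7.2 item 3 and the or-reading of 8.2.6 give opposite answers, and these are the patients for whom reinduction was written.

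In the middle row, item 2 read literally also opposes item 3. The protocol does separate the two ideas. Section 4.1 says that resistance needs an accumulation of mutations, and that the EC50 "starts to show a clinically significant increase from five mutations". Where a genotype is available, the exclusion criteria in 6.2 bar only mutations that reduce susceptibility to LPV/r, so a patient in the middle row can be enrolled.

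**Step 2: day of the confirming sample**, counted from the first value.

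- 7.2: day 15
- 8.2.6: day 14 or later
- 8.2.3 and 8.2.5: day 14 or earlier

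Overlaps:

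- 7.2 with 8.2.6: day 15 (compatible)
- 8.2.6 with 8.2.3/8.2.5: day 14 only
- 7.2 with 8.2.3/8.2.5: none
- all three: none

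If 15 days is read loosely as two weeks, all three share day 14 and no other day. A retest on day 5, for example, obeys the visit section but meets neither failure definition, even on the loose reading.

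**Step 3: what the interval does.** It settles whether failure counts as confirmed. It does not choose between failure and reinduction, which depends on Step 1.

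**The case against.** The strongest defence is that the document uses LPV/r resistance as its working criterion almost throughout. The rest of item 2 speaks of needing a regimen without LPV/r. Item 3 opens as a qualification of item 2. The closing bullets of 7.2 sort monotherapy patients only by lopinavir resistance, and the genotype clause of 8.2.6 is limited to mutations that preclude LPV/r monotherapy. This largely stands. A reader might infer from item 2 and the five-mutation remark that every patient with one to four mutations receives opposite instructions. The documents do not compel that, because items 2 and 3 can be read together and the EC50 remark is background, not a trial criterion. The defence does not remove the and/or in 8.2.6, which lets viral load alone define failure. The heading of 8.2.6 also mentions modification, but its text says that study medication is stopped.

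On the interval, the retest instruction applies to any value above 50 copies/mL, is not itself a failure definition, and does not forbid a further sample. That stands, so a prompt retest need not make failure impossible to establish. The written intervals still conflict.

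A reader might also set 7.2, where "a follow-up visit will be scheduled 4 weeks after the end of study visit", against 8.2.4, where "a telephone follow-up call will be made after 30 days of last visit study to monitor safety". These are not contradictory. The visit follows the design of rescue treatment for declared failures. The call is a safety contact for anyone viraemic, or with an ongoing adverse event, at the last visit. One patient can receive both.

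Annex 1 may resolve some of this. Because 8.2.3 calls its content suggestions, it cannot be assumed to override the written criteria.

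Finally, the virological endpoint in 8.1.2 (below 50 copies/mL at week 24, with failure as a confirmed value above 500) uses no genotype, so the conflict does not change its definition. It does affect who is still in the study to be measured.

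**Conclusion.** The point holds as an internal contradiction. 7.2 item 3 and 8.2.6, read with or, classify the same non-resistant rebounding patient in opposite ways, and the three confirmation intervals share no day when read literally. Item 2 adds a looser genotype phrase that can be reconciled with item 3 but should not need interpretation. The consequences are for withdrawal, per-protocol membership and the source of the quality-of-life value, in the monotherapy arm.

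The size cannot be derived from the protocol. A reader might take the 81% undetectable on monotherapy in section 4.1 and compute (1 − 0.81) × 260 = 49.4 patients. That figure does not size the problem. It comes from another study at 48 weeks, it counts loss of undetectability and not confirmed values above 500 copies/mL, and it says nothing about genotype. Nor should one infer that the interval mismatch by itself turns a failure into a reinduced non-failure.

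The conclusion rests on the written sections alone, with the Annex 1 flow chart unseen, and on the or-reading of 8.2.6 being one that a site could reasonably adopt.

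**What to change.** Reconcile items 2 and 3 of 7.2 with 8.2.6 so that a single genotype and viral-load criterion separates therapeutic failure from reinduction, and replace the and/or with an unambiguous conjunction. State one confirmation interval and use it identically in 7.2, 8.2.3, 8.2.5 and 8.2.6. Check the Annex 1 flow chart against the result. Which version stands is for the sponsor and investigators to decide.

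For the analysis, record the genotype result and the dates of both viral loads, and classify every case by the agreed rule whichever section the site followed.

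The cost is a wording amendment under the procedure in 11.4. No tests are needed beyond those already planned.
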